# Antenatal preventative pelvic floor muscle exercise intervention led by midwives to reduce postnatal urinary incontinence (APPEAL): protocol for a feasibility and pilot cluster randomised controlled trial

**DOI:** 10.1186/s40814-022-01185-y

**Published:** 2022-10-22

**Keywords:** Pelvic floor muscle exercises, Pregnancy, Postnatal, Urinary incontinence

## Abstract

**Background:**

Antenatal pelvic floor muscle exercises (PFME) in women without prior urinary incontinence (UI) are effective in reducing postnatal UI; however, UK midwives often do not provide advice and information to women on undertaking PFME, with evidence that among women who do receive advice, many do not perform PFME.

**Methods:**

The primary aim of this feasibility and pilot cluster randomised controlled trial is to provide a potential assessment of the feasibility of undertaking a future definitive trial of a midwifery-led antenatal intervention to support women to perform PFME in pregnancy and reduce UI postnatally.

Community midwifery teams in participating NHS sites comprise trial clusters (*n* = 17). Midwives in teams randomised to the intervention will be trained on how to teach PFME to women and how to support them in undertaking PFME in pregnancy. Women whose community midwifery teams are allocated to control will receive standard antenatal care only.

All pregnant women who give birth over a pre-selected sample month who receive antenatal care from participating community midwifery teams (clusters) will be sent a questionnaire at 10–12 weeks postpartum (around 1400–1500 women). Process evaluation data will include interviews with midwives to assess if the intervention could be implemented as planned. Interviews with women in both trial arms will explore their experiences of support from midwives to perform PFME during pregnancy. Data will be stored securely at the Universities of Birmingham and Exeter.

Results will be disseminated through publications aimed at maternity service users, clinicians, and academics and inform a potential definitive trial of effectiveness. The West Midlands–Edgbaston Research Ethics Committee approved the study protocol.

**Discussion:**

Trial outcomes will determine if criteria to progress to a definitive cluster trial are met. These include women’s questionnaire return rates, prevalence of UI, and other health outcomes as reported by women at 10–12 weeks postpartum. Progress to a definitive trial however is likely to be prevented in the UK context by new perinatal pelvic health service, although this may be possible elsewhere.

**Trial registration:**

10.1186/ISRCTN10833250. Registered 09/03/2020

## Background

Pregnancy and birth are the main risk factors for urinary incontinence (UI) [1]. Prevalence of UI at around 30 weeks gestation has been reported as 31% in nulliparous and 42% in parous women [2]. Postpartum prevalence ranges from 30% in the first 3 months to up to 47% in the first 12 months postpartum [3]. Between two-thirds to three-quarters of women may still experience UI symptoms 12 years after delivery [4] placing a large burden on women’s health and quality of life [5], with pressure on NHS resources and wider societal costs [6].

Despite experiencing UI, many women ‘suffer in silence’ as they are embarrassed or accept symptoms as normal after having a baby, despite evidence that pelvic floor muscle exercises (PFME), if performed correctly in pregnancy, can reduce risk of developing UI after giving birth. A Cochrane review of effectiveness of PFME for prevention and management of urinary and faecal incontinence in pregnant and postnatal populations [7] included 46 trials with a total of 10832 women. Data were analysed according to whether PFME interventions were for prevention of UI (pregnant women without prior UI) or for treatment (pregnant or postnatal women symptomatic of UI) or mixed prevention/treatment trials. In prevention trials, pregnant women without prior UI randomised to PFME teaching and supervision were 29% (RR 0.71,95% CI 0.54 to 0.95) less likely than women randomised to no PFME or usual antenatal care to report UI up to 6 months after giving birth. Mixed prevention/treatment trials were of moderate quality with a possibility of similar reduction in postpartum UI (RR 0.73, 95% 0.55 to 0.97). There was no clear evidence on whether PFME is effective for treating pregnant or postnatal women symptomatic of UI.

Currently most pregnant women without prior UI do not benefit from effective PFME, due to lack of information and support about how to undertake these. Furthermore for antenatal PFME to be effective, teaching should be delivered through a structured training programme (ensuring PFME is performed correctly and regularly) [8] since information provision alone is seldom enough to support long-term (exercise) behaviour change [9].

The Royal College of Midwives and Chartered Society of Physiotherapy published a joint statement recommending that all pregnant women should be offered evidence-based information and advice on PFME [10] but did not address overcoming barriers to implementation on the part of midwives or women [11]. A major policy review by NHS England recognised the importance of maternal perinatal pelvic floor health. The NHS Long-Term plan [12] includes specific recommendations to improve access to postnatal physiotherapy and importance of training and support in pelvic floor health for clinicians, including midwives, working with women. Despite recently updated NICE guidelines for routine antenatal care making no specific mention of PFME in pregnancy [13], guidance does include a link to NICE guidance on pelvic floor dysfunction [14] which recommends that for women using the maternity services, information on preventing pelvic floor dysfunction should be offered at all antenatal and postnatal contacts. The guideline also recommends pelvic floor dysfunction is included as part of the training syllabus for all relevant healthcare professionals [14].

### Feasibility and pilot trial rationale

Translational research focuses on moving discoveries from ‘bench to bedside’ to close the translational gap [15]; however, closing this first translational gap is insufficient to demonstrate full clinical impact of an intervention. In UK maternity services, there is a ‘second translational gap’ between evidence generated and implementation into practice. With a high prevalence of UI following birth, lack of implementation of evidence to prevent UI through use of PFME has a serious cumulative impact on women’s health. Conversations with NHS consultant midwives when developing our study confirmed a lack of consistency in how PFME information was offered in their maternity units, with no formal training to support midwives to deliver structured PFME advice. Of 103 local antenatal women we surveyed to ask about health advice they were offered by their midwives, only 50% could recall any information about PFME and of those who did, half did not perform PFME for a range of reasons. Implementation of PFME would require individual and collective action of women, clinicians, maternity services and organisations, funders and policymakers [16].

The NIHR funded Antenatal Preventative Pelvic Floor Exercises And Localisation (APPEAL) programme includes several linked work packages (WP). The first WP explored perceived organisational, health professional and individual barriers and enablers to implementation of PFME in current UK practice [16]. It involved a critical interpretive synthesis of systematically identified primary quantitative, qualitative studies and research syntheses of women’s and HCPs attitudes, beliefs, or experiences of implementing PFMT [11]. This paper describes the protocol for the feasibility and pilot cluster trial being undertaken as the final WP which is reported in line with the Standard Protocol Items Recommendations for Interventional Trials (SPIRIT) [17].

## Methods and analysis

The primary aim of this feasibility and pilot cluster randomised controlled trial is to assess the feasibility of undertaking a future definitive trial of a midwifery-led antenatal intervention to support women to perform PFME in pregnancy to reduce UI postnatally and assess intervention acceptability to midwives and the women they support.

Specific objectives include feasibility of undertaking a future definitive trial, informed by return rates of questionnaires sent to all women who give birth over a pre-selected 1-month period when they are 10–12 weeks postpartum, prevalence of UI and other health outcomes and feasibility of implementing the trial intervention by midwives at routine antenatal care contacts (Table 1).

**Table 1 Tab1:** Feasibility and pilot trial objectives

• Provide training for community midwife teams randomised to the intervention arm to encourage the incorporation of a PFME care package into their usual antenatal care	
• Assess if training, intervention implementation and trial processes are acceptable to midwives	
• Assess if midwife characteristics (e.g. years qualified) are similar across trial arms for feasibility	
• Assess questionnaire return rates from women at 10–12 weeks postpartum overall and in both trial arms to inform feasibility and estimate sample size for a full-scale RCT	
**•** Assess characteristics of women overall and within trial arms who return questionnaires compared with all those who gave birth in the same midwifery teams over the same study period but did not respond, using anonymised routine data	
• Assess if baseline characteristics collected following birth (self-reported UI at pregnancy commencement, maternal and obstetric characteristics collated from antenatal booking, labour and birth data) are similar across trial arms to inform feasibility	
• Assess women’s practice of PFME before, during and after pregnancy using women’s postnatal questionnaire and interview data	
• Assess prevalence of UI and faecal incontinence at 10–12 weeks postpartum using women’s questionnaire data to inform the sample size calculation for a full-scale RCT	
• Assess midwife support for PFME in both trial groups using qualitative interviews with midwives, women, and women’s questionnaire data to inform feasibility	
• Undertake any necessary revisions to the APPEAL training package and following this, recommend roll-out by midwives to all pregnant women as part of the NHS Long-Term Plan	

The trial schematic is shown in Fig. 1.

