### Intervention

Intervention components and materials to support behaviour change are underpinned by the Behaviour Change Wheel theoretical framework and the Behaviour Change Technique Taxonomy (version 1) [18, 19] in line with the Medical Research Council’s guidance for developing and evaluating complex interventions (https://www.bmj.com/content/374/bmj.n2061).

Due to strict COVID-19 policies at NHS sites, midwife training will be provided via online interactive video-conferencing with small groups of midwives. Two research midwives will lead and facilitate initial training sessions lasting approximately 2 h. Training handbooks will be sent to intervention cluster midwives before their training. The training package will include an interactive session with vignettes and role-play to enable midwives to raise and discuss the importance of a healthy pelvic floor, benefits of performance of PFME to prevent UI, and a video of how to teach women about PFME. Information is presented on pelvic floor muscle anatomy and function; muscle exercise training principles (physiology), a stepped approach to assessing and teaching the correct muscle contraction, setting an individualised PFME training programme, information on how to screen for serious incontinence problems and criteria for referral.

Following training, midwives will initially introduce the topic of pelvic floor health at the antenatal ‘booking’ appointment or as early as possible after this. At this appointment the midwife will explain to the woman that she will receive a resource pack to help her perform PFME. Each resource pack will include an APPEAL leaflet with PFME information, a link to APPEAL developed videos, a card with links to recommended Apps to download to support PFME performance, and some promotional items (e.g. APPEAL logo stickers) to use as reminders. Women will be asked at all subsequent antenatal appointments about PFME progress (with adaptation of personalised PFME training programme where necessary) and any problems with PFME or UI symptoms.

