Each intervention cluster will include a midwife ‘champion’ from the team who will receive additional training on how to support and manage women whose UI symptoms may be more severe or giving cause for concern, including appropriate referral pathways. Champions will also provide reminders and advice for midwives in their team. Midwives will be given 2 to 3 months (depending on date of their training) to practice implementing the PFME intervention into their routine care.

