#### Randomisation

Midwifery community-based teams (clusters) will be randomised in a 1:1 ratio to standard care only or standard care plus intervention. A minimisation algorithm implemented in Microsoft Excel by the study statistician will be used to ensure approximate balance over the following variables:Midwifery team size defined by number of births (≤median monthly bookings vs >median monthly bookings)NHS maternity unit

A ‘random element’ will be included in the minimisation algorithm, so that each cluster has a probability of being randomised to the opposite treatment that they would have otherwise received.

Blinding of midwives providing care will not be possible due to the nature of the intervention. Women receiving antenatal care will not explicitly be blinded but the PFME support they experience will be the usual care provided by their midwives. Those responsible for conducting the trial analysis (but not the process evaluation) will be blind to allocation.

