#### Women’s questionnaires at 10–12 weeks

The questionnaire pack will include a request to return the completed questionnaire to the unit Research Midwife in a pre-paid self-addressed envelope. A £10 voucher will be given to ‘thank’ women who return completed questionnaires. Table 2 shows data collection processes and timing.

Responses from completed questionnaires will be entered by a Research Midwife employed by the NHS maternity unit. The Research Midwives will provide a list of the hospital/NHS numbers of the women who grant permission for their maternity records to be accessed to their local IT Department to obtain information on:Woman’s age, ethnicity, parity, onset of labour (spontaneous or induced), mode of birth (spontaneous vaginal, instrumental, caesarean section), anaesthetic/analgesia used, perineal trauma, episiotomy, and duration of active second stage.Baby’s gestation at birth, birthweight, and head circumference.

**Table 2 Tab2:** APPEAL data collection process and timing

Outcome/data	Timing of data capture	Process
Midwifery team characteristics (clusters); midwife experience of trial processes	Various times throughout the cluster trial process	Number of births per team, number and grades of midwives per team and team location, number of women/births per team from NHS trust managers/community-team leads. Interviews with individual midwives in both study arms.
Health outcomes & PFME performance	Questionnaire follow up of all women in participating clusters at 10-12 weeks postpartum.	Overseen by local NHS trust Research Midwives. If no response to initial follow up, questionnaire resent. If no response after a further two weeks, other options will include sending a text message reminder
Data from women’s maternity records	On return of consent in women’s questionnaire.	Extracted by local trust Research Midwives from maternity records.
Data from telephone/online interviews with women from both trial arms	Interviews with 10-15 women from each trial arm	A sample of up to 30 women who agreed to be approached. Interviews to qualitatively explore their experiences of receiving (or not) information and advice about doing PFME during pregnancy; and to explore any possible contamination between arms.

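### Labour and birth data are counted as baseline characteristics for judging whether the arms are similar, although they arise after randomisation and after antenatal exposure to the intervention

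*Protocol article*

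**What the plan says.** Table 1 of the protocol article (Methods and analysis) sets the objective of assessing whether baseline characteristics, gathered after the birth (self-reported UI at the start of pregnancy, "maternal and obstetric characteristics collated from antenatal booking, labour and birth data) are similar across trial arms to inform feasibility". Booking items, labour and birth events, and a self-report about early pregnancy are thus placed under one label.

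The section on women's questionnaires lists what is taken from the maternity record. Besides age, ethnicity and parity it includes onset of labour, "mode of birth (spontaneous vaginal, instrumental, caesarean section), anaesthetic/analgesia used, perineal trauma, episiotomy, and duration of active second stage", and infant data.

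On timing, the Randomisation section states: "Midwifery community-based teams (clusters) will be randomised in a 1:1 ratio to standard care only or standard care plus intervention". Under Intervention, trained "midwives will initially introduce the topic of pelvic floor health at the antenatal ‘booking’ appointment or as early as possible after this". Contact then continues: "Women will be asked at all subsequent antenatal appointments about PFME progress", and the same sentence adds any problems with the exercises or UI symptoms. Before that, "Midwives will be given 2 to 3 months (depending on date of their training) to practice implementing the PFME intervention into their routine care".

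The first progression criterion (Outcomes) asks that the return rate should not be likely to cause substantial bias. This may be shown by a high overall return rate, by responders in the two arms having similar baseline characteristics, or by both.

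**The concern.** A baseline comparison between randomised arms asks whether the groups were alike before the intervention could act. An item can answer that only if its value was settled by then. Labour and birth events were not. A difference in them could reflect prior imbalance, selective questionnaire return, or something that followed from allocation, and the comparison cannot separate these. Similarity is no safer, because components of opposite sign can cancel.

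UI at the start of pregnancy is a different case. The state precedes the woman's exposure, but her report of it comes after birth. Women are not explicitly blinded, and intervention midwives are told to ask about UI symptoms during pregnancy, so the report may be prompted differently in the two arms.

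At stake is the feasibility judgement. The earlier pilot study had a return rate of 31.3% (243 of 777). If the trial's rate is similar, the high-return route to the first criterion may not be open, and similarity of responders would carry it. The criteria are deliberately unquantified, so the choice of items bears directly on the judgement.

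**Working it through.** **Plan's own figure.** The only precision figure is the maximum confidence interval width of 17.2% for the return rate. With 17 clusters of 82 (n = 1394), ICC 0.10, rate 50% and a t-distribution on 16 df, the design effect is 1 + 81 × 0.10 = 9.1. The width is 2 × 2.12 × √(0.25 / 1394 × 9.1) = 17.1%, which agrees to 0.1 point. Nothing below depends on it or changes it.

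**Step 1: order of events, from the sections cited.**

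| Item | When its value is settled | When it is recorded | Can it show prior comparability? |
|---|---|---|---|
| Age, ethnicity, parity, booking items | Before the intervention, or at the visit where it is first raised | Maternity record | Yes |
| UI at the start of pregnancy | Before the woman's exposure | Self-report after birth | Yes, subject to recall |
| Onset of labour, mode of birth, analgesia, perineal trauma, episiotomy, second stage; infant data | At birth, after team allocation and antenatal contact | Maternity record | No |

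The timing of the UI report at 10–12 weeks is inferred. Table 1 says only that it is collected after birth, and the 10–12-week questionnaire is the only one to women that the article describes.

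**Step 2: what a between-arm difference among responders contains.**

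observed difference = prior difference + difference arising after allocation + difference due to who responds (+ difference in recall, for self-reports)

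For age, ethnicity and parity the second term is zero by construction, so the comparison speaks to prior imbalance and selection. For labour and birth items the second term is unknown. It need not be large, or even present, for the comparison to lose its meaning as a baseline check; it is enough that it cannot be ruled out.

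**Step 3: illustration for recalled UI (all inputs assumed; none is in the documents).** Let P be the true proportion with UI at the start of pregnancy, equal in both arms, Se the recall sensitivity and Sp the specificity. The reported proportion is P × Se + (1 − P) × (1 − Sp). With Sp = 0.95 in both arms, the difference is P × (difference in Se).

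| P | Se 0.90 | Se 0.80 | Se 0.70 | Difference from Se 0.90 |
|---|---|---|---|---|
| 10% | 13.5% | 12.5% | 11.5% | 1 to 2 points |
| 20% | 22.0% | 20.0% | 18.0% | 2 to 4 points |
| 30% | 30.5% | 27.5% | 24.5% | 3 to 6 points |

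A different assumption, over-reporting in one arm only, gives other values. If 20% truly had UI and an extra 5% to 10% of the remaining 80% report it, the gap is 0.80 × 0.05 = 4 points to 0.80 × 0.10 = 8 points. Either arm could be the higher one. The tables show only that comparable arms can look unlike.

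**The case against.** Much of the case on the other side stands.

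- **Disclosure.** Table 1 says openly that these characteristics are collected after birth. That discloses when they are collected, but it does not separate items fixed earlier from events of labour.
- **Effect on birth outcomes.** A reader might infer that antenatal exercise alters mode of birth or perineal trauma. The documents report an effect on postnatal UI only. The point here rests on timing and needs no such effect.
- **UI enquiry in control teams.** A reader might infer that only intervention women are asked about UI symptoms. The article prescribes this for intervention midwives and does not describe what control midwives ask. It also cites guidance that pelvic floor information be offered at all maternity contacts, and it plans to assess contamination. Differential recall is therefore possible, not established.
- **Link to progression.** The criterion does not cite the Table 1 list. Table 1 is, however, the only place where the article says what its baseline characteristics are. The criterion is and/or, is weighed with others and goes to the Trial Steering Committee, so this group of items could not decide progression alone.
- **A separate selection check.** Another Table 1 objective compares responders with non-responders, overall and within arms, using anonymised routine data. Within an arm all women share the allocation, so labour and birth data are legitimate there. This limits how far selection could go unseen, but it does not repair the between-arm comparison.
- **Visibility.** Small shifts would be hard to see. At 31% return, 0.31 × 1400 = 434, or 217 per arm. With about 8.5 clusters per arm (25.5 women each), 20% prevalence and the return-rate ICC of 0.10 borrowed, the standard error is √(0.16 / 217 × 3.45) = 5.0 points, which gives roughly ±12 points per arm. That tempers the recall concern. It does not affect the classification of labour and birth items.

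**Conclusion.** The classification is wrong for labour and birth data and should be corrected. They arise after allocation and after antenatal exposure, so they cannot serve as evidence that the arms, or the responders in them, were comparable beforehand. This follows from the article's own sequence of events; how long individual women were exposed does not matter to it.

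For UI at the start of pregnancy the conclusion is weaker. It is a valid baseline state measured late, with possible differential recall of unknown size and direction; 1 to 6 points (or 4 to 8) holds only under the assumptions shown. A reader might conclude that it should be dropped from the comparison. The documents do not support that: it is the only described measure of initial UI status, and the Background distinguishes women with and without prior UI.

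The consequence is confined to the feasibility and bias judgement. The analysis is descriptive, without hypothesis testing between arms, and no covariate adjustment is described, so a prediction that a later trial would adjust for mediators has no footing in the text.

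**What to change.** - In Table 1 and the first progression criterion, limit the between-arm comparison of baseline characteristics to items fixed before the intervention: age, ethnicity, parity and antenatal-booking items.
- Report labour, birth and infant data by arm in a separate table headed as post-randomisation data. They may still be used in the within-arm comparison of responders with non-responders.
- Keep UI at the start of pregnancy in the between-arm comparison, labelled as postnatal recall, with a note that recall may differ by arm.

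The cost is a change of wording and table layout. No new data are needed.
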